### Apparatus

#### Overview

Stress level was measured both objectively (physiological stress reaction) and subjectively (appraisal of the perceived stress in ecological momentary assessments [EMAs]). Possible stressors were also identified both as subjective perception via questionnaires and objectively by matching physiological stress responses to concurrent ambient conditions, such as noise, interruptions, or specific activities. We compared the objective stress levels to the daily staffing, occupancy level, and other daily changing factors of a hospital ward.

To this end, a combination of wearable and ambient sensors that can measure the physiological (objective) stress reaction as well as possible stressors (causes of stress) is being used. The prototypical setup consisted of a smart wristband, a smartphone, near-field communication (NFC) tags, and Raspberry Pis equipped with microphones to record interruptions (incoming telephone calls) and unexpected tasks (calls from patients). The setup can be seen in Figure 2 and Figure 3. At the end of the study, it will be possible to characterize a normal working day of a palliative caregiver more precisely in terms of physical and psychological stress. The perceived burden will be correlated with bed occupancy and the numbers of patient admissions, discharges, and deaths per day as well as influence of the duty roster design (including the staffing) and frequency of interruptions by telephone or a patient’s bell.

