### Sample and Recruitment

The PCU at UMR, with its 14 beds, is the largest PCU in Mecklenburg-Western Pomerania, Germany. It employed 13 full-time nurses and 5 part-time nurses who work in a 3-shift system during the study implementation in 2021. Study participants had to be older than 18 years, their working time had to have a minimum of 20 hours per week, they had to have proficiency in written and spoken German, and they had to be employed at the palliative care unit at the Rostock University Medical Centre (inclusion criteria). Exclusion criteria comprised of nonconsenting capacity and nonfulfilment of all inclusion criteria. For the DiPa study, all 18 nurses working in the UMR PCU, who partly specialize in palliative care, were invited in December 2020 to participate in the study by presenting the procedure and aims of the project in a lecture as well as in a written inquiry. The measurement period for each participant was 6 weeks allowing for a total measurement duration of 3 months.

A power analysis was not conducted as the population was prespecified (N=18), rendering the need for an accruing sample. In the end, 12 nurses agreed to participate, resulting in a participation rate of 67% (12/18).

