### Procedures

After enrollment, each participant received thorough instruction on how to use the technical equipment. On the same day, each participant was interviewed separately to define their expectations and attitudes toward the DiPa study. Interviews were conducted by UMR staff who were not involved in the study (ie, a research assistant or a member of the central research center of the UMR). The answers were recorded during the interview and transcribed afterward to allow for an evaluation by independent raters to reduce bias and ensure data privacy. In addition, the participants completed the questionnaire on their perception of stressors and stress, including patient-associated stressors, working environment, team-associated stressors, and resources.

Participants were instructed to conduct the measurements during every shift. At the beginning of the shift, the participants gathered their equipment from their locker, put on the wristband, and picked up the smartphone. By turning on the wristband, a digital questionnaire appeared automatically on the smartphone’s display, welcoming the participant and asking for their current stress level as well as sleep quality of the previous night. Further free-text annotations were also possible. Participants then stored the smartphone in the pocket of their scrubs and began their workday.

Participants were instructed to use the smartphone to scan the corresponding NFC tag whenever entering a patient’s room. To this end, a green NFC tag with an arrow was placed on each patient room door. This event was thus recorded on the smartphone. Analogously, a red NFC tag was scanned when leaving the room. This not only recorded the event but also prompted a short questionnaire that was displayed on the smartphone’s screen, asked for their current stress level, and included a free-text space.

Special recurring processes on the PCU like daily visits, weekly and daily team meetings attended by nurses and physicians, and patient interviews had their own individual NFC tags denoting the start and end.

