In parallel to data recording by the wristband and smartphone, the study team collected and analyzed data about the nurses (eg, how many worked in the ward per shift, length of work experience in years, and if they had the additional designation of “palliative care nurse,” as we expected an influence of workload for each participant). The second focus was patient-associated factors, especially the average, minimum, and maximum patient age and number of occupied beds per day. Because the PCU treats many critical ill patients with life-limiting diseases, we also thought it could be important to analyze the number of deaths per day.

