The acceleration data were fused to a 3D vector by applying the following equation:

All algorithms for data extraction were written in Python using Jupyter Notebooks and the *Pandas*, *Numpy*, *SciPy*, *Matplotlib*, and *NeuroKit2* libraries.

For stress detection analysis, all stress events marked with a button press will be identified, and windows surrounding this event will be extracted and averaged, leading to one value per stress event per participant. Analogously, the windows surrounding a scan of the NFC tag “relaxation” and the baseline windows will be extracted and averaged as well. Descriptive and inferential statistical analyses will be applied using IBM SPSS Statistics 30. Weighted ANOVAs for correlated samples will be computed to compare the stressful events and the baseline for each physiological parameter.

To examine the predictability of experiencing stress, the subjective ratings given in the EMA will be used as ground truth. Surrounding the EMA, data windows will be extracted from the data for each physiological parameter. A linear regression will be computed with the subjective stress level (EMA) as the dependent variable and entering the means of the physiological variables (HR, HRV, tonic EDA, phasic EDA, temperature, and acceleration) as independent variables. Artificial intelligence approaches will be used to analyze the data where appropriate.

With the data for daily occupancy of patients and the total number of nurses on the same day, we will be able to calculate the relationships of these 2 variables with stress. The minimum occupation level according to the recommendation from the German Society for Palliative Medicine (*Deutsche Gesellschaft für Palliativmedizin*) on staffing in palliative wards [30] of 1.4 nurses per patient will be used as a cutoff to create two subgroups of “well-staffed” and “under-staffed.”

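### Staffing is recorded per shift, but stress is related to the whole day's nurse count; this loses precision and makes a real staffing effect easier to miss

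*Protocol article*

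**What the plan says.** Four statements in the Methods of the protocol article bear on this.

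- **How staffing is recorded.** Procedures lists, among the data gathered about the nurses, "how many worked in the ward per shift". Occupancy in the same paragraph is daily: "number of occupied beds per day".
- **When stress is measured.** Sample and Recruitment describes "13 full-time nurses and 5 part-time nurses who work in a 3-shift system during the study implementation in 2021". Procedures adds: "Participants were instructed to conduct the measurements during every shift". Ratings and signals therefore belong to a particular shift.
- **How staffing is analysed.** Data Analyses reads "With the data for daily occupancy of patients and the total number of nurses on the same day" and continues "we will be able to calculate the relationships of these 2 variables with stress". The Overview under Apparatus also speaks of the daily level: "We compared the objective stress levels to the daily staffing, occupancy level, and other daily changing factors of a hospital ward".
- **What the analysis is for.** The same Overview intends to examine the "influence of the duty roster design (including the staffing" component, alongside occupancy and interruptions.

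No section says that a rating or signal is linked to the staffing of its own shift. Strengths and Limitations states that there is no analysis plan stratified by shift.

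**The concern.** The exposure is named at a coarser unit than either the outcome or the recorded data. A nurse on a thinly staffed late shift gets the same staffing value as a colleague on that day's well-covered early shift. A roster decides how nurses are spread over shifts, so a day count removes much of the contrast that the roster question needs. For a shift that runs past midnight, it is also unclear which day's count applies.

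At stake is how informative the staffing analysis can be. The study has 12 participants and no power analysis, so it has little precision to spare.

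**Working it through.** The article gives no effect size, power or sample size for this analysis, so there is no figure of its own to reproduce. The check is how much a day count weakens an association that acts through own-shift staffing.

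**Inputs**
- Three shifts per day, 18 nurses employed, 14 beds (Sample and Recruitment).
- Nurses counted per shift, beds counted per day (Procedures).
- Cutoff of 1.4 nurses per patient (Data Analyses).
- Assumed: stress depends on own-shift staffing S1 with slope b; the three shifts have equal variance v and pairwise correlation rho. The article gives no value for rho, so a range is shown.

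**Correlation.** Let T = S1 + S2 + S3.
- Cov(S1, T) = v(1 + 2rho)
- Var(T) = 3v(1 + 2rho)
- Corr(S1, T)² = [v(1 + 2rho)]² / [v × 3v(1 + 2rho)] = (1 + 2rho)/3

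The correlation of stress with T is therefore the correlation with S1 multiplied by sqrt((1 + 2rho)/3). The information needed to make up for this is about 3/(1 + 2rho) times as much.

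| rho (assumed) | Correlation multiplied by | Information needed |
|---|---|---|
| -0.25 | 0.41 | 6.0 times |
| 0 | 0.58 | 3.0 times |
| 0.5 | 0.82 | 1.5 times |
| 0.9 | 0.97 | 1.07 times |
| 1 | 1.00 | 1.0 times |

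A negative rho would arise if a nurse added to one shift is taken from another.

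**Slope**
- On the day count: b × v(1 + 2rho) / [3v(1 + 2rho)] = b/3.
- On the mean count per shift, T/3: b × [v(1 + 2rho)/3] / [v(1 + 2rho)/3] = b.

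The factor of one third is only a change of scale.

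**Simulation.** With 200,000 simulated days and b = -1, the correlation ratios were 0.57, 0.82 and 0.97 at rho = 0, 0.5 and 0.9. The slopes were about -0.33 on the day count and between -0.99 and -1.00 on the mean per shift. Both agree with the formulas.

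**Illustration (assumed rosters, 14 patients).** Rosters of 4/4/4, 5/4/3 and 6/4/2 all total 12 nurses, which is 12/14 = 0.86 per patient for the day. Per shift, the ratio runs from 2/14 = 0.14 to 6/14 = 0.43. The day count cannot tell these three days apart.

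**Cutoff.** 1.4 × 14 = 19.6 nurses, more than the 18 employed. At full occupancy no single shift could reach it.

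**The case against.** - **The per-shift counts may still be used.** Procedures says the nurse data were analysed as well as collected, and Data Analyses does not say that day counts replace them. This stands in part: a reader might infer that the per-shift counts are thrown away, and the text does not say so. But the only staffing variable the article links to stress is the daily one, and it is named in two sections. This is a stated choice of variable, not a detail left to a fuller plan.
- **The effect is not diluted towards zero.** A reader might infer from b/3 that a small or null staffing effect is to be expected. That does not follow, because the slope on mean nurses per shift is b under the same assumptions. This objection stands in full: what is lost is correlation and precision.
- **The size of the loss is unknown.** This is correct. It depends on rho and on equal variances, neither of which is in the article, and it vanishes as rho approaches 1.
- **A day count matches the daily bed count and avoids mixing staffing with shift type.** Both are true. The first does not prevent refining the nurse count alone; the second calls for a covariate.
- **The staffing subgroups.** A reader might infer that they too are formed from day counts. The article gives the cutoff without saying which nurse count is the numerator, so this cannot be settled. Moving the cutoff to single shifts would not work either, as the 19.6 against 18 comparison shows.
- **The analysis is secondary.** The primary outcome is feasibility, and the lack of shift stratification is disclosed. This limits the weight of the point but does not remove the mismatch.

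**Conclusion.** The mismatch is real and rests on the article's own words: staffing is counted by shift, stress is measured within a shift, and the two are to be related through a count for the day. If own-shift staffing is what acts on stress and the shifts vary equally, the correlation keeps between 0.58 and 0.97 of its value for rho from 0 to 0.9, and less if rho is negative. Only perfectly parallel staffing across the three shifts costs nothing. The consequence is that a real effect is more easily missed. The documents do not support a biased slope per mean nurse per shift, an expected null, or a firm figure for the loss. The point should be corrected, but it concerns a secondary analysis of a feasibility study.

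**What to change.** In Data Analyses, replace the day's nurse count in the staffing–stress analysis with the number of nurses on duty in the shift in which the rating or signal was recorded. Keep daily occupied beds as the occupancy measure, assign each night shift to the date on which it starts, and include shift type as a covariate.

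Do not apply the 1.4 nurses-per-patient cutoff to single shifts. State which nurse count it refers to, and reconcile that unit with the staffing variable before forming the two subgroups.

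The cost is small. The per-shift counts have been collected and the physiological data carry time stamps, so no new data are needed. The linkage should be done at the independent institute that analyses individual-level data, so that the employing hospital still receives only averaged results. The one statistical price is the adjustment for shift type, needed because staffing and workload may both differ between shifts.

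### The 1.4 nurses-per-patient cutoff has no stated unit; applied to nurses present per day it is out of reach on a full or nearly full ward, so the staffing split is likely to be lopsided and to track occupancy

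*Protocol article*

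**What the plan says.** The Data Analyses section introduces the staffing analysis as follows: "With the data for daily occupancy of patients and the total number of nurses on the same day", the relationships of these two variables with stress will be calculated. The next sentence takes a minimum from a professional society's staffing recommendation and states that the level "of 1.4 nurses per patient will be used as a cutoff to create two subgroups of" well-staffed and under-staffed. It does not say whether the figure means nurses present per day, nurses present per shift, or posts employed per bed or per patient.

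Sample and Recruitment describes the ward: "The PCU at UMR, with its 14 beds", and "It employed 13 full-time nurses and 5 part-time nurses who work in a 3-shift system during the study implementation in 2021". The total is given as "all 18 nurses working in the UMR PCU". Procedures lists what was recorded about staffing and patients, including "how many worked in the ward per shift" and the "number of occupied beds per day".

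**The concern.** The cutoff and the ward's own figures do not fit together. A ratio of 1.4 nurses per patient on a full 14-bed ward needs more nurses in one day than the ward employs across all three shifts. If the rule is followed as the text reads, nearly every well-occupied day falls into the under-staffed group whatever the roster looked like, and the few well-staffed days are mostly days with few patients.

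The two-group comparison would then have little contrast in staffing, and any difference in stress between groups could reflect patient numbers. The article says the results are to guide preventive measures (Future Directions), so a label of under-staffed that follows largely from the choice of cutoff could be carried into recommendations about the ward.

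**Working it through.** The article takes 1.4 from an outside recommendation and derives no figure from it, so there is no plan figure to reproduce. The one internal total agrees: 13 + 5 = 18 nurses.

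**Inputs from the article:** cutoff 1.4; 14 beds; 18 nurses (13 full-time, 5 part-time); three shifts.

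**Not in the article, assumed below:** part-time fraction, shifts per week, absence, mean occupancy.

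**1. Nurses present per day, no assumptions.** Nurses needed = 1.4 × patients.
- 14 patients: 1.4 × 14 = 19.6, more than 18. With all 18 present, 18/14 = 1.29.
- 13 patients: 1.4 × 13 = 18.2, more than 18. With all 18 present, 18/13 = 1.38.
- 12 patients: 1.4 × 12 = 16.8. With all 18 present, 18/12 = 1.50.

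At 13 or 14 patients no roster of the employed nurses reaches the cutoff. At 12 it is reachable only if at least 17 of the 18 work the same day.

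**2. Nurses present per day, with rostering.** Highest occupancy that meets the cutoff = nurses present / 1.4, rounded down.
- Favourable to the plan (all 18 full-time, five shifts a week, no leave): 18 × 5/7 = 12.9 per day on average; 12.9/1.4 = 9.2, so 9 or fewer patients (64% of beds).
- Part-time at 0.5 to 0.9 of a post, five shifts a week, 15% to 25% absence: posts = 13 + 5 × 0.5 = 15.5 to 13 + 5 × 0.9 = 17.5. Present per day = 15.5 × 5/7 × 0.75 = 8.3 to 17.5 × 5/7 × 0.85 = 10.6. Dividing by 1.4 gives 5.9 to 7.6, so at most 5 to 7 patients. On a full ward the ratio would be 8.3/14 = 0.59 to 10.6/14 = 0.76.

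**3. Possible size of the well-staffed group.** Share of days at or below the limiting occupancy, assuming that the 14 beds fill independently and the nurse count is the same every day:

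| Nurses present | Limit (patients) | Mean occupancy 60% | 70% | 80% | 90% |
|---|---|---|---|---|---|
| 8 | 5 | 6% | 0.8% | <0.1% | <0.1% |
| 9 | 6 | 15% | 3% | 0.2% | <0.1% |
| 10 or 11 | 7 | 31% | 9% | 1% | <0.1% |
| 12 | 8 | 51% | 22% | 4% | 0.2% |
| 13 | 9 | 72% | 42% | 13% | 0.9% |

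The share depends heavily on occupancy. It is small at 80% or more with up to 12 nurses present, and can be substantial at 60% to 70%.

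**4. Other readings of 1.4.**
- *Nurses present per shift:* the numerator is smaller than the day total, so the cutoff is harder to reach.
- *Posts per bed:* at most 18/14 = 1.29, or 15.5/14 = 1.11 to 17.5/14 = 1.25 with the assumed part-time fractions. Every day is under-staffed and there is no contrast.
- *Posts per occupied bed:* the numerator is essentially fixed. The boundary lies at 15.5/1.4 = 11.1 to 17.5/1.4 = 12.5 occupied beds (18/1.4 = 12.9 by headcount). Both groups may be populated, but the split is then a cut on occupancy and says nothing about who was on duty.

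**The case against.** A reader might infer that the cutoff can never be met on this ward, that the well-staffed group will be empty, and that the study cannot answer its staffing question. The article does not support any of these.

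- The ratio divides by patients, not beds, so days with fewer patients can qualify; at 12 patients 18/12 = 1.50.
- The article gives neither mean occupancy nor daily attendance. The group sizes in the table rest on assumed values, independent bed filling and a constant nurse count; correlated admissions or a varying roster would change them.
- If 1.4 means posts per occupied bed, both groups could be well filled. The objection is then to what the split measures, not to an empty group.
- The same section also plans to relate occupancy and nurse numbers to stress without any split, and the Apparatus overview plans to relate perceived burden to bed occupancy and to the duty roster, including staffing. Those analyses do not depend on the cutoff.
- The primary outcome is feasibility (Potential Outcomes and Impact); this grouping is secondary, and the article already concedes limited subgroup insight with 12 participants.

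All of this stands, and it limits the size of the point. It does not rescue the split. This is not detail that a condensed article leaves to an analysis plan: the cutoff and the quantities paired with it are stated, and under each of the readings examined the grouping is either likely to be lopsided, constant, or a proxy for occupancy. Nor can the unit be traced from the article, because the reference number given for the staffing recommendation, [30], is also the one given for the SPIRIT guideline under Usage of Study Guidelines.

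**Conclusion.** The concern holds in limited form. What follows from the article's own figures, without assumptions, is that a cutoff of 1.4 nurses present per patient per day is unreachable at 13 or 14 patients. With rostering it is met only at 9 or fewer patients under the most favourable assumption used here, and at about 5 to 7 or fewer under assumed part-time fractions and 15% to 25% absence. A very small well-staffed group is therefore likely unless occupancy was low, but its actual share cannot be determined from the article. Even where low occupancy fills that group, it would mainly identify days with few patients.

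The unsplit analyses of occupancy and staffing are unaffected, as is the primary feasibility outcome. This should be fixed before the staffing comparison is run; it does not threaten the study's main aim.

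**What to change.** Do not form the comparison groups by applying 1.4 to daily head counts. Make the continuous ratio of patients to nurses on duty the staffing exposure, built from the per-shift nurse counts and daily occupied beds that Procedures says were collected. The analysis should account for shift type and for repeated measures within nurse and within day, since nurses working the same shift share the exposure value.

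If the 1.4 benchmark is kept for description, state its unit, match the numerator to that unit, correct the reference so that the source can be traced, and report the number of days in each group.

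The cost is wording and analysis code; no new data are needed, and the article reports that final analysis is still to be completed. What is lost is the simple contrast between meeting and not meeting the recommendation as an inferential comparison.

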### Usage of Study Guidelines

We structured our study protocol using the SPIRIT (Standard Protocol Items: Recommendations for Interventional Trials) guidelines [30].

### Ethical Considerations

The ethics committee of the University of Rostock approved the study (approval A 2020-0295). Data protection is ensured by providing participants with their own lockers to store their devices, gathering data using pseudonyms only, and analyzing raw data at the Fraunhofer IGD exclusively (sharing only group means with the UMR, which employs the participants).

All possible participants received information in writing assuring them that participation was voluntary, that the choice of not participating would yield no harmful consequences, and that they could withdraw from the study at any time if they no longer wished to participate. Each participant had the possibility to ask further questions. They were asked by a study nurse, so the inviter and the participant were on the same hierarchy level, lowering any possible pressure that the nurses might have felt to participate. They were assured in speech and writing that they did not have to fear professional consequences or disadvantages if deciding against participating in the study.

